## Abstract

**Background:**

Chronic conditions are responsible for a growing burden of morbidity, mortality, and cost globally. Despite widespread recognition of the need for preventive care, general practice remains underresourced and primarily focused on treatment. Digital health interventions (DHIs) present a scalable solution to support person-centered preventive care, but evidence regarding the feasibility and acceptability of multirisk consumer-facing interventions in general practice remains limited.

**Objective:**

This study (ePREVENT-360) aims to evaluate the feasibility, acceptability, sustainability, and preliminary impact on health activation of a consumer-facing DHI, THRIVE (Tailored Health Risk Insights for Vital Empowerment) in Australian general practices.

**Methods:**

A mixed methods, pre-post feasibility study will be conducted in 5 general practices across New South Wales, Queensland, and Victoria. Adult consumers aged 30 to 65 years will use the THRIVE digital platform to receive chronic condition risk assessments, health scores, and action plans. Quantitative data will include engagement metrics, surveys, and chronic condition risk scores. Qualitative semistructured interviews with consumers and clinicians will provide data about acceptability, engagement, and sustainability. Quantitative data will be analyzed using descriptive and multilevel regression methods, while qualitative data will be analyzed thematically.

**Results:**

The study has secured funding in 2024 through an Australian General Practice Research Foundation and Hospital Contribution Fund of Australia Research Foundation Health Services Research Grant. Consumer recruitment commenced in December 2025. Recruitment of the 5 participating general practices was completed in March 2026. As of April 2026, all clinician preintervention interviews have been completed, and consumer recruitment has commenced, with 25 consents obtained. Data collection is ongoing, with follow-up expected to be completed by December 2026. Outcomes will inform the iterative refinement of interventions and future trial designs to assess effectiveness.

**Conclusions:**

This study will address a key evidence gap in the digital prevention space by evaluating the feasibility, acceptability, and sustainability of a multicondition DHI embedded in general practices. The findings will support the development of a larger adaptive controlled trial and inform future implementation.

## Introduction

### Background and Rationale

Chronic conditions, including cardiovascular disease, type 2 diabetes, and common cancers, contribute to a substantial and growing global health and economic burden [1-3]. These conditions arise from complex interactions between modifiable (eg, smoking, inactivity, and poor diet) and nonmodifiable (eg, age, ethnicity, and family history) risk factors [4]. Importantly, over 17 million premature deaths each year are attributable to preventable causes [1,2], highlighting the critical role of primary and secondary prevention in reducing disease burden and improving population health outcomes.

While the cost-effectiveness and long-term benefits of prevention are well established, many health systems continue to struggle to deliver equitable, timely, and comprehensive preventive care—particularly within general practice [5-7]. General practice serves as the frontline of health care, encompassing health promotion, early detection and intervention, and the management of acute and chronic conditions [8]. In Australia, despite national policy commitments to preventive health [9]; systemic barriers, such as fragmented services and inadequate financial incentives for preventive activities; and chronic underinvestment in general practice continue to impede the implementation of effective prevention models [10-13].

Participation in preventive services remains suboptimal in Australia, with only 52% of eligible women participating in breast cancer screening [14] and only 42% of eligible adults undertaking bowel cancer screening [15]. Routine recording of risk factor data for common chronic conditions, such as cardiovascular disease and type 2 diabetes, is also inconsistent. This limits the feasibility of proactive risk identification, with data recorded for only 49% and 24% of the population, respectively [16,17]. These gaps underscore the need for scalable, system-wide strategies to increase access to and engagement with preventive care. Digital health interventions (DHIs) are a promising avenue to strengthen preventive care delivery, yet their acceptability, engagement, and feasibility in real-world general practice settings remain underexplored.

### Challenges to Effective Prevention at the Individual Level

Supporting sustained improvements in lifestyle risk factors is a significant challenge, with effective and scalable solutions yet to be fully established. High health literacy [18-20] and patient activation [21-29] have been strongly associated with improved lifestyle risk profiles. Patient activation is an individual’s knowledge, skills, and confidence in managing their health [30,31]. Emerging evidence suggests that patient activation is most strongly associated with improved health behaviors, increased participation in screening and preventive care, and better overall health outcomes than health literacy alone [21,22,24]. Despite its potential, the role of activation in the primary prevention of chronic conditions remains underexplored [21,22,25,29]. Thus, identifying and evaluating effective strategies to enhance and sustain patient activation in general practice is a pressing area for future research.

### Digital Health and Emerging Opportunities

The COVID-19 pandemic catalyzed the rapid adoption of DHIs [32]. These interventions are diverse, ranging from automated SMS reminders to complex interventions integrated with electronic health systems that use natural language processing, machine learning, and artificial intelligence [33,34]. DHIs offer considerable potential to collect and track real-time individual health data and to personalize health promotion, health education, and behavior change content to individual needs and risk profiles [35]. Sustained behavior change addressing lifestyle risk factors is an essential aspect of effective prevention, and DHIs are recognized to be an effective vehicle for persuasion compared to human-delivered interventions [36]. Despite this promise, most existing digital health research has centered on narrow, condition- or risk factor–specific applications—such as behavior change interventions (eg, weight loss [37], smoking cessation [38]), condition management (eg, diabetes self-monitoring [39-41]), or clinician-facing tools (eg, decision support or telehealth [42,43]). In contrast, there is comparatively little evidence examining the role of consumer-facing DHIs designed to deliver comprehensive primary and secondary prevention [39,40,42], meaning the potential of these technologies to enable real-time monitoring of population-level health indicators remains unrealized [39,42,44].

Despite the substantial contribution of social, environmental, and behavioral factors to the risk of developing common conditions, these indicators are not routinely captured or used meaningfully to enable precision prevention and monitoring [44]. Persistent barriers to digital health adoption, including a lack of trust, particularly among groups with low digital literacy and overlapping social determinant risk factors, remain to be addressed [33,45]. There are critical gaps in the current landscape, including the need for rigorously testing digital interventions to empower consumers to understand and act on their risk in general practice. Furthermore, understanding whether low health activation functions as an obstacle to engagement with digital interventions is an important research priority. Addressing these gaps is essential to developing scalable, sustainable models of preventive care [46].

### Objectives

The primary objectives of ePREVENT-360 are to assess the feasibility of the THRIVE (Tailored Health Risk Insights for Vital Empowerment) digital intervention for adults in Australian general practices by (1) examining factors that influence clinician and consumer engagement, (2) evaluating the intervention’s acceptability, and (3) exploring perceptions of the intervention’s sustainability. The secondary objective is to assess the preliminary effectiveness of THRIVE on consumer activation, self-rated health, and chronic disease risk scores.

## Methods

### Study Design

This protocol is reported according to the SPIRIT (Standard Protocol Items: Recommendations for Interventional Trials) 2025 guidelines (Checklist 1) [47]. The ePREVENT-360 study is a mixed methods, pre-post feasibility trial designed in accordance with the UK Medical Research Council (MRC) framework [48] for evaluating complex interventions. The study will be guided by 2 complementary theoretical models to inform the assessment of user acceptability: the extended unified theory of acceptance and use of technology 2 (UTAUT2) [49,50] and the theoretical framework of acceptability [51].

### Settings

The study will be conducted in 5 general practices in New South Wales, Queensland, and Victoria, Australia. Practices will be recruited through local primary health care organizations (primary health networks), practice-based research networks, relevant professional organizations, and snowballing. Practices with a minimum of 5 general practitioners will be prioritized to ensure sufficient organizational capacity to support study onboarding, patient recruitment, and study processes. Larger practices typically have more stable administrative support, larger patient volumes, and established prevention and management workflows, making them more suitable for inclusion.

Practices will be purposively selected to ensure geographic diversity across metropolitan, regional, and rural locations. Each participating practice will be asked to nominate 1 general practitioner or general practice nurse to act as the study champion. This champion will receive comprehensive study information and lead the practice’s involvement. General practices will provide informed consent, including an agreement to promote study participation to eligible patients and clinicians.

### Participants

#### Consumer Sampling and Recruitment

A convenience sample of consumers will be recruited from participating practices. Eligible consumers will be adults aged 30 to 65 years, who can speak English and have regular access to an internet-enabled digital device, such as a smartphone, tablet, or computer. This age range was selected to maximize preventive potential, targeting individuals most likely to benefit from lifestyle changes and screening engagement before the onset of chronic conditions.

Each practice will recruit consumer participants over a 3-month recruitment period. The recruitment process will be multifaceted. Primarily, brochures or posters with QR codes will be displayed in waiting and consulting rooms, allowing individuals to access information via their mobile phones while they are waiting. This QR code links to a webpage where people can register their interest, receive study information, and complete the consent form. Additionally, study information will be disseminated via practice newsletters and/or emails if available. To minimize burden on the participating practices, clinicians are not expected to recruit consumers; however, individual clinicians can opportunistically encourage consumers to consider participation.

#### Clinician Sampling and Recruitment

All general practitioners and general practice nurses from participating practices will be invited to take part in the preintervention and postintervention interviews and the postintervention survey. Clinician participation will be entirely voluntary. Study information, including a QR code link to the survey or consent form, will be emailed to potential participants by the practice. Additionally, a QR code linking to the survey or consent form will be displayed in the practice staff areas.

### Sample Size

#### Consumer Participants

As a feasibility study, this trial is not powered to detect statistically significant differences in outcomes. Instead, the sample size was determined to allow for the estimation of key feasibility indicators with acceptable precision [52]. If approximately 50% of participants who consent complete the THRIVE health assessment, with a 10% margin of error at a 95% CI, a minimum sample size of 187 consumers will be required.

In line with previous general practice research [53-57], a cluster adjustment was applied to the sample calculation using an intracluster correlation coefficient of 0.05 [53-57]. With an anticipated 5 participating practices and a design effect of 1.95, allowing for an estimated 15% dropout rate, the adjusted sample size requirement will be 215 consumers. Therefore, each practice is expected to recruit at least 43 participants.

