#### Engagement

Engagement will be measured using THRIVE usage logs, which automatically record participants’ interactions with the platform. Based on these behaviors over the 6-month study period, participants will be classified into 1 of 5 engagement levels (Figure 2). Individuals who consent but do not initiate or complete the risk assessment will be classified within the “no use” engagement category. This group will be included in follow-up surveys and purposive qualitative sampling to capture barriers to engagement.

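### The design effect of 1.95 fits 20 consumers per practice, but the plan recruits 43, so the expected precision is about ±12 points rather than the stated ±10.

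*Protocol article*

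**What the plan says.** All the figures are in the Protocol article, Methods, Sample Size, Consumer Participants. That section says the trial is not powered to detect differences and is sized instead for the precision of key feasibility indicators. The indicator used is assessment completion among consenters, which is assumed to be about one half. For that proportion the plan states its requirement as follows: "with a 10% margin of error at a 95% CI, a minimum sample size of 187 consumers will be required".

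The next paragraph describes a cluster adjustment "using an intracluster correlation coefficient of 0.05" and continues: "With an anticipated 5 participating practices and a design effect of 1.95, allowing for an estimated 15% dropout rate, the adjusted sample size requirement" is 215 consumers. From this it concludes that "each practice is expected to recruit at least 43 participants".

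On who is counted, the Engagement section under Outcomes says: "Individuals who consent but do not initiate or complete the risk assessment will be classified within the" no-use category. These consenters therefore stay in the denominator of the completion proportion.

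**The concern.** A design effect depends on the number of consumers per practice as well as on the ICC. The section gives the ICC, the design effect, the number of practices and the recruits per practice, so the four can be checked against one another, and they disagree. The design effect appears to have been worked out from the cluster size before inflation and not updated once the inflated total was spread over the same 5 practices.

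This matters because precision is the only quantitative justification offered for the size of the study. Completion belongs to engagement, a component of the primary feasibility outcome. If the precision is misstated, readers and the planners of the later trial will expect a narrower interval than the design can give under its own ICC.

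**Working it through.** **Inputs**, all from the Consumer Participants section: p = 0.50, d = 0.10, 95% confidence (z = 1.96), ICC = 0.05, design effect 1.95, 5 practices, 15% dropout, totals of 187 and 215, and 43 per practice. Equal practice sizes are assumed.

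**Reproducing the plan's figures**

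- Unclustered size: z² p(1 − p)/d² = 1.96² x 0.25/0.01 = 96.04, rounded up to 97.
- With the design effect: 96.04 x 1.95 = 187.3, the stated 187. So 187 already contains the cluster adjustment.
- With the dropout allowance: 187 x 1.15 = 215.05, the stated 215; 215/5 = 43.

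**Cluster size implied by 1.95**

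The standard formula is DE = 1 + (m − 1) x ICC. Solving for m gives m = 1 + 0.95/0.05 = 20. This matches the unclustered requirement over 5 practices (97/5 = 19.4, rounded up). The figure of 20 is not printed in the article; it is inferred from the two values that are.

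**Design effect at the planned cluster sizes**

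Half-width = z x √(0.25 x DE/n).

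| Consumers analysed | Per practice | DE | Effective n | 95% half-width (normal) |
|---|---|---|---|---|
| 215 | 43 | 1 + 42 x 0.05 = 3.10 | 215/3.10 = 69.4 | ±11.8 points |
| 187 | 37.4 | 1 + 36.4 x 0.05 = 2.82 | 187/2.82 = 66.3 | ±12.0 points |

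The first row applies to the completion proportion, because consenters who do not complete remain in the denominator. It is also the more favourable of the two.

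**With t on 4 df.** Using 5 − 1 = 4 degrees of freedom, the multiplier is 2.776 instead of 1.96: 2.776 x √(0.25/69.4) = 0.167, or about ±17 points.

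**Can more consumers in the same 5 practices restore ±10?**

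- As m grows, effective n approaches 5/0.05 = 100, where the half-width is 1.96 x √(0.25/100) = ±9.8 points.
- Setting effective n to 96.04 gives n = 96.04 x 0.95/(1 − 96.04 x 0.05/5) = 91.24/0.0396, or about 2,300 consumers (about 460 per practice).
- Keeping 20 per practice, 187 consumers would need 187/20 = 9.35, so about 10 practices.

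**Which ICC would rescue the stated figures?**

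- A design effect of 1.95 at m = 43 needs ICC = 0.95/42 = 0.023.
- ±10 points at n = 215 with the normal quantile needs DE = 215/96.04 = 2.24, so ICC = 1.24/42, or about 0.03.
- Both are below the 0.05 that the plan adopts.

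**Dropout.** 215 x 0.85 = 183, which is below 187; preserving 187 after 15% dropout would take 187/0.85 = 220. The gap is 5 people in total.

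**The case against.** The strongest reply is that the loss is small and changes no stated decision. With the normal quantile the shortfall is 1.8 points. The article disclaims power. Its Progression Criteria are flexible, are read alongside qualitative findings and print no threshold for completion. The ICC is itself a planning assumption, and at about 0.03 or below the ±10 would roughly hold. All of this stands and limits the weight of the point. It does not remove the contradiction: the plan chose 0.05, and nothing in the article supplies a cluster size of 20, another formula or another ICC that would yield 1.95 at 43 per practice.

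It can also be said that ±17 combines the design-effect error with a separate choice of quantile. That is fair. The like-for-like comparison is ±12 against ±10, and ±17 is what a particular small-cluster interval would add.

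Two stronger readings are tempting and are not supported:

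- A reader might infer that the reported completion rate will be over-confident. A planning design effect does not enter the observed interval. Over-confidence would require an analysis that ignores practice, and the article prescribes no such interval; Primary Outcome Analyses gives only descriptive statistics for the feasibility end points and leaves detail to a SAP that is not shown.
- A reader might take 187 as a wrong number because the cluster adjustment is described after it. The text never calls it unadjusted, and the arithmetic shows the adjustment is already in it. The order of the sentences is unclear, but the figure is not wrong.

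The dropout slip is real but minor. It does not affect completion, although an allowance remains sensible for the post-intervention survey.

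**Conclusion.** The point holds as an internal contradiction in the sample-size section. Under the plan's own ICC, number of practices and recruits per practice, the design effect is 3.10 rather than 1.95, and the expected 95% half-width around 50% is about ±12 points instead of ±10 (about ±17 if t on 4 df is used).

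This rests on the standard design-effect formula, equal recruitment across the 5 practices, all 215 consenters being counted, and an ICC of 0.05. The size of the discrepancy is modest, and it does not show that the study is too small for its feasibility purpose. It does mean that the one precision claim supporting the sample size is wrong as written.

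**What to change.** Keep the target of 215 and make these changes:

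1. Restate the precision: 215 consumers in 5 practices (43 each), ICC 0.05, design effect 3.10, effective sample size about 69, 95% CI half-width about ±12 points (about ±17 with t on 4 df).
2. State that the unclustered size is 97 and that 187 already includes the design effect of 1.95 used at that step.
3. Report the completion proportion with a confidence interval that accounts for practice, adding a line to the SAP if it does not already say so.
4. Note that multiplying 187 by 1.15 does not preserve 187 after 15% dropout, and that dropout does not reduce the denominator for completion. The target need not change on that account.

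The cost is rewording in one section and possibly one line in the SAP. No further participants or practices are needed. The downside is that the published precision becomes less favourable.

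### The design effect of 1.95 fits 20 consumers per practice, not the planned 43; at the assumed ICC of 0.05 the expected 95% margin is about ±12 points, not ±10

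*Protocol article*

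**What the plan says.** Under Methods, Sample Size, Consumer Participants, the Protocol article says the study is not powered for differences and bases the sample on the precision of feasibility estimates. The target quantity is the proportion completing the assessment: "If approximately 50% of participants who consent complete the THRIVE health assessment", then "with a 10% margin of error at a 95% CI, a minimum sample size of 187 consumers will be required".

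The next paragraph introduces clustering: "a cluster adjustment was applied to the sample calculation using an intracluster correlation coefficient of 0.05". It continues "With an anticipated 5 participating practices and a design effect of 1.95", "allowing for an estimated 15% dropout rate", and arrives at an adjusted requirement of 215. The section ends: "Therefore, each practice is expected to recruit at least 43 participants".

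The cluster size behind 1.95 is not given, and the requirement before clustering is not shown.

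**The concern.** Under the usual formula, the ICC and the number of consumers per practice together fix the design effect. The section states an ICC of 0.05, a design effect of 1.95 and 43 consumers per practice, and these three do not fit together. If 1.95 is too small for the planned practices, the ±10-point margin is too optimistic.

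This matters because precision for the completion proportion is the only quantitative reason given for the sample size, and engagement is a component of the primary feasibility outcome. The study is also meant to inform the design of a later trial, so a design effect worked out at the wrong cluster size could be carried forward.

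A smaller matter is order. The 187 is presented as following from the proportion, margin and confidence level alone, with the cluster adjustment described afterwards. A reader cannot see which step produced which total.

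**Working it through.** **Inputs**, all from the Consumer Participants part of the Sample Size section: proportion p = 0.50; margin d = 0.10; 95% confidence (z = 1.96); ICC = 0.05; 5 practices; design effect 1.95; dropout 15%; totals 187 and 215; 43 per practice.

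**1. Reproducing the plan's totals.**
- Unclustered: n0 = z² p(1 − p)/d² = 1.96² x 0.25/0.01 = 96.04.
- With the stated design effect: 96.04 x 1.95 = 187.3, the printed 187.
- With dropout: 187 x 1.15 = 215.05, the printed 215.
- Per practice: 215/5 = 43.

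Both totals reproduce. The 187 therefore already contains the cluster inflation, and only dropout separates 187 from 215. (Dividing by 0.85 would give 220; the difference is small and is not part of this point.)

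**2. The cluster size behind 1.95.** With design effect DE = 1 + (m − 1) x ICC, setting 1.95 = 1 + (m − 1) x 0.05 gives m = 20. That is the unclustered sample spread over 5 practices: 96.04/5 = 19.2, or 97/5 = 19.4, rounded up to 20.

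**3. The design effect at the planned size.**
- 43 per practice: 1 + 42 x 0.05 = 3.10.
- 187/5 = 37.4 per practice: 1 + 36.4 x 0.05 = 2.82.

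**4. The precision that follows**, with margin = 1.96 x √(0.25/n_eff) and n_eff = N/DE:

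| Consumers analysed | Per practice | DE | Effective n | 95% margin |
|---|---|---|---|---|
| 187, DE as printed | – | 1.95 | 96 | ±10.0 points |
| 187, DE at the planned size | 37.4 | 2.82 | 66 | ±12.0 points |
| 215, DE at the planned size | 43 | 3.10 | 69 | ±11.8 points |

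The 215 row is the favourable case. Under Outcomes, Engagement, people who consent but do not complete the assessment are kept as a no-use category, so they stay in the denominator.

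**5. What would reconcile the figures.**
- A design effect of 1.95 at 43 per practice needs ICC = 0.95/42 = 0.023 (0.95/36.4 = 0.026 at 37.4 per practice).
- With 5 practices, n_eff approaches 5/0.05 = 100 as N grows, so the margin cannot fall below 1.96 x √(0.25/100) = ±9.8 points.
- Reaching ±10 with 5 practices needs N = n0(1 − ICC)/(1 − n0 x ICC/5) = 96.04 x 0.95/(1 − 0.9604), about 2,300 consumers or 460 per practice.

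**6. Sensitivity to the ICC** (values other than 0.05 are assumptions; range over 215 to 187 analysed): 0.01 gives ±8.0 to ±8.4; 0.02 gives ±9.1 to ±9.4; 0.05 gives ±11.8 to ±12.0; 0.10 gives ±15.2 to ±15.4.

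**The case against.** The strongest reply is that little turns on this. The shortfall is about 2 points. The study disclaims power. The Progression Criteria section sets out a flexible three-level framework, and the article states no numeric threshold for assessment completion; the printed cut-offs concern acceptability. That stands, and it limits the seriousness of the point. It does not make the printed margin right, since precision is the justification the plan chose.

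A second reply is that the true ICC may be smaller. At 0.02 the ±10 target would be met. This also stands, but only as a condition: the plan adopted 0.05, and the shortfall holds at that value. The alternative-ICC sensitivity analyses under Secondary Outcome Analyses concern the exploratory multilevel models and do not correct the sample-size statement.

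Three stronger readings are tempting, and the document does not support them.
- A reader might infer that 187 is labelled as a figure before clustering, that 1.95 should be applied to it (187 x 1.95 = 365), and that 215 is therefore a second numerical error. The article attaches no such label, and both totals reproduce from the printed inputs. The 365 arises only if the inflation is applied twice. The fault is one of order.
- A reader might take the true margin to be about ±17, which is what a t value of 2.776 on 4 degrees of freedom gives at 215. The plan's own calculation uses z = 1.96 and promises no small-cluster interval, so ±17 is at most an optional sensitivity figure.
- A reader might conclude that the plan ignores clustering when it reports the completion proportion. The article does not say so, and how that interval is calculated is ordinary content for the statistical analysis plan, which is not shown.

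**Conclusion.** The point holds. At ICC 0.05, a design effect of 1.95 belongs to 20 consumers per practice, and the plan recruits 43, where it is 3.10. The expected 95% margin for a 50% completion proportion is about ±11.8 points with 215 consumers (±12.0 with 187), against the stated ±10. Nothing elsewhere in the article repairs this.

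The conclusion rests on the plan's own ICC, 5 practices of roughly equal size, the standard design-effect formula and a normal quantile. It would not hold if the ICC were about 0.023 or lower. Because the limit is the number of practices, adding consumers is not a practical way to reach ±10.

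This should be corrected, but it does not threaten the study: the shortfall is modest, and no stated decision depends on ±10 rather than ±12.

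**What to change.** Keep 215 and rewrite the sample-size text in the order in which the figures arise:
- 96 consumers before clustering, for 50% ± 10 points at 95% confidence;
- 187 identified as already cluster-adjusted (96 x 1.95), with 1.95 stated to be the design effect at 20 per practice and ICC 0.05;
- 215 after the 15% dropout allowance, or 43 per practice;
- a design effect of 3.10 at 43 per practice and ICC 0.05, an effective sample size of about 69, and an expected 95% margin of about ±12 points in place of ±10.

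The authors may add, as an optional sensitivity figure, that a t-based margin on 4 degrees of freedom would be about ±17 points.

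The cost is wording only, with a slightly less favourable statement of precision and no extra participants. The article reports 25 consents by 17 April 2026 and says the analysis plan will be preregistered before data extraction, so the correction can be made before any data are examined.
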